## Abstract

Reactive balance, a critical automatic movement pattern in response to a perturbation, is directly linked to fall prevention in older adults. Various exercise interventions have been broadly performed to improve reactive balance and thus prevent falls. Curiously, aquatic exercises have been suggested as an effective balance intervention and a safer alternative to exercises on dry land yet the efficacy of aquatic exercises on reactive balance has not been formally investigated. The present clinical trial aims to identify if skills acquired during aquatic exercise are more effectively transferred to a reactive balance task than land exercise. This study is designed as a double-blinded, randomized controlled clinical trial. Forty-four older adults aged 65 years or above who meet the eligibility criteria will be recruited and randomized into an aquatic exercise group or land exercise group. Each group will participate in the same single bout intervention that includes a ball throwing and catching task. A modified lean-and-release test will be implemented on land immediately before, after, and one week after the single bout intervention. The outcomes will include reaction time, rapid response accuracy, and mini-BESTest scores obtained from stepping and grasping reactions. All statistical analyses will be conducted using an intention-to-treat approach. Our conceptual hypothesis is that participants in the aquatic exercise group will demonstrate more improved outcome scores in the lean-and-release test when compared to those in the land exercise group. The results of the present study are expected to provide evidence to support the benefits of aquatic exercises for improving reactive balance in older adults. Further, participants may find aquatic exercises safer and more motivating, thus encouraging them to participate in further aquatic exercise programs.

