Hence, the current study aims to compare measures of reactive balance control after a single bout intervention on land and in chest-deep water. There have been several studies presenting greater enhancements in dry-land balance performance, specifically in static and proactive balance measures, such as Berg Balance Scale [26], 8-Foot Up and Go Test [27], and Functional Reach Test [28] following AE versus land exercise (LE) in healthy older adults. As none of the previous trials included any measures of reactive balance, the current study will specifically focus on improvements in reactive balance capacity after a single bout intervention. During aquatic exercises, water resistance produces overload during movements, and hydrostatic pressure constantly facilitates sensory awareness and motor functions. Further, the confidence level is augmented in the safer aquatic environment, which in turn increases variability in movement systems and maximizes neuromuscular adaptations. Thus, we hypothesize that participants in an AE group will present greater improvements (e.g., more accurate and rapid responses) during the reactive balance assessment compared to those in a LE group. The greater improvements will be demonstrated by faster response speed (i.e., shorter reaction time), greater accuracy alongside faster response speed (e.g., higher rapid response accuracy), and greater quality of response (e.g., higher mini-BESTest score). The Mini Balance Evaluation System Test (mini-BESTest) is a comprehensive clinical balance assessment, which evaluates four different balance control systems. This tool is commonly used by clinicians and practitioners and well known to be advisable to identify the disordered systems underlying balance control and design specific rehabilitation approaches in varied age and patient populations [29]. In this study, the second section (Reactive Postural Control) will be utilized to score the quality of compensatory balance responses.

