### Statistical analysis

Dependent variables included in the statistical analyses will be: 1) hand contact time during REACH; 2) foot-off time during STEP; 3) foot contact time during STEP; 4) rapid response accuracy during RANDOM; 5) mini-BESTest score of REACH; 6) mini-BESTest score of STEP; 7) mini-BESTest score of RADOM. There are two independent variables including the groups (AE vs. LE) and time (pre vs. post vs. follow-up).

The baseline differences in demographic data and all dependent variables between AE and LE groups will be analyzed using independent samples t-tests for data with a normal distribution and using the non-parametric Mann-Whitney U-test for data without normal distribution. On confirming the assumptions of the normal distribution (Kolmogorov–Smirnov test) and homogeneity of variances (Levene’s test), dependent variables will be compared using 2 (group: AE, LE) × 3 (time: pre, post, follow-up) repeated-measures (RA) analysis of variance (ANOVA) with group as a between-group factor and time as a within-group factor. If baseline differences of the dependent variables occur, baseline values will be included as covariates. If the assumptions are violated, Kruskal-Wallis one-way ANOVA will be used for nonparametric variables. In addition, post-hoc analyses will be conducted using Tukey post hoc test or Mann-Whitney U test. The meaningfulness of statistical differences will be reported using Cohen’s d effect sizes (ES) and confidence intervals (95%) for the parametrical variables and probability of superiority for dependent samples (PS_dep_) for the nonparametric variables [41]. Alpha will be set *a priori* at .05 for all statistical analyses. Missing data will be handled using multiple imputation, and all statistical analyses taking an intention-to-treat approach will be conducted with SPSS version 25 (SPSS Inc., Chicago, IL, USA).

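### Seven unranked dependent variables are each tested at .05 with no primary outcome, no adjustment across variables and no success rule, so the chance of some false positive is about 11–30%

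*Protocol article*

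**What the plan says.** The Statistical analysis section opens with the list of variables: "Dependent variables included in the statistical analyses will be: 1) hand contact time during REACH; 2) foot-off time during STEP". It continues with foot contact time during STEP, rapid response accuracy during RANDOM, and mini-BESTest scores for the three blocks, ending at "7) mini-BESTest score of RADOM". None is marked as primary.

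The analysis is stated once for all of them: "dependent variables will be compared using 2 (group: AE, LE) × 3 (time: pre, post, follow-up"), as a repeated-measures ANOVA. Kruskal-Wallis is the fallback if assumptions fail, and post-hoc testing is by Tukey or Mann-Whitney U. Alpha is set "at .05 for all statistical analyses".

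Other sections do not supply a ranking. The Abstract says: "The outcomes will include reaction time, rapid response accuracy, and mini-BESTest scores obtained from stepping and grasping reactions". The Problem statement says: "The greater improvements will be demonstrated by faster response speed (i.e., shorter reaction time"), and then adds accuracy alongside speed, and quality of response. The Sample size calculations section uses the Berg Balance Scale, which is not among the seven variables.

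**The concern.** The alpha rule is a positive instruction. Anyone who follows it will run seven parallel tests, each at 5%, in support of one hypothesis, that aquatic exercise (AE) transfers better to reactive balance than land exercise (LE). Nothing says which result decides the question, or whether one, several or all must be significant. The sample size calculation does not settle it by implication either, since it rests on a scale that this trial does not measure.

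The text therefore permits one significant variable out of seven, picked out after the data are seen, to be reported as confirming the hypothesis. The error rate of that claim would be several times 5%.

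**Working it through.** **Inputs**

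- Alpha per test: .05 (Statistical analysis).
- Number of dependent variables: 7 (Statistical analysis).
- Tests of the hypothesis per variable: one group-by-time interaction in a 2 × 3 ANOVA (Statistical analysis).
- Enrolled: 22 per group (Sample size calculations).
- Correlation ρ between variables: not given. Assumed equal for all pairs and varied from 0 to 0.9.
- Correlation between time points: not given. Assumed 0.6 in the ANOVA simulation, and varied from 0.3 to 0.9 where times are tested separately.

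**Stated rate.** The only error rate in the article is .05 per test. It is the error rate of the main claim only if one test decides that claim.

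**Step 1: seven tests, independent.** P(at least one false positive) = 1 − (1 − α)^k = 1 − 0.95^7 = 0.302.

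**Step 2: seven tests, correlated.** The variables come from the same participants and partly from the same movements, so independence is the upper end. The table gives the chance of at least one false positive when no variable has a true effect. The first column treats the seven tests as correlated two-sided z tests. The second simulates seven 2 × 3 ANOVAs with 22 per group and counts the interaction only.

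| ρ | z tests | ANOVA interaction |
|---|---|---|
| 0 | 30% | 30% |
| 0.3 | 27% | 28% |
| 0.5 | 23% | 24% |
| 0.7 | 18% | 19% |
| 0.9 | 11% | 12% |

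The two methods agree to about one percentage point.

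**Step 3: errors in the hypothesised direction.** Only a result favouring AE supports the hypothesis. For a single AE–LE contrast at two-sided .05, the nominal rate in that direction is 2.5%. With seven independent contrasts it is 1 − 0.975^7 = 0.162. With ρ = 0.3, 0.5, 0.7 and 0.9 it is 14%, 11.5%, 9% and 6%. The 2 × 3 interaction has two degrees of freedom and no sign, so these figures apply to the directional contrast that would be reported from it.

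**Step 4: if post and follow-up were tested separately, without first requiring a significant interaction.** That makes 7 × 2 = 14 tests. Over between-time correlations of 0.9 to 0.3, the chance of at least one false positive is 36–46% at ρ = 0.3, 31–40% at ρ = 0.5 and 24–32% at ρ = 0.7.

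**Step 5: what the post-hoc tests control.** Tukey adjusts among comparisons within one variable, so it does nothing across the seven. The Mann-Whitney option carries no stated adjustment at all.

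**The case against.** **The hypothesis may be conjunctive.** The Problem statement joins speed, accuracy and quality with an *and*. If all had to succeed there would be no inflation. This stands in part: the article nowhere says that any one variable suffices, and that reading is permitted by the text, not stated in it. But the article does not say that all must succeed either. Speed and quality also contain three variables each, so a rule at the level of the three domains would still leave a choice within two of them.

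**Each time point is not separately tested at .05.** A reader might infer fourteen .05 tests and an error rate near 40%. The parametric plan does not support that, because pre, post and follow-up enter one model per variable, with Tukey afterwards. The 24–46% range applies only to ungated testing by time, which the nonparametric route could allow.

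**Every ANOVA effect might be counted.** A reader might count group, time and interaction for each variable. Time main effects do not compare AE with LE and cannot support the hypothesis, so they do not belong in the count.

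**A primary outcome may be named elsewhere.** The article cites a registry record, and a full protocol or analysis plan may exist. None can be checked here, so the statement that there is no primary outcome holds for this article only. The article's own rule, the same alpha for everything, would still need correcting.

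**The study is small, and the variables are listed in advance with effect sizes and confidence intervals.** This helps transparency. It does not define the error rate of the main claim, and the article presents a directional hypothesis with a formal power calculation, not an exploratory study.

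**Conclusion.** The concern holds in a limited form. Following the article as written, with one interaction test for each of seven unranked variables, the chance of at least one false positive is about 11–30% two-sided, and 18–27% at correlations of 0.7 to 0.3. For a false result favouring AE it is about 6–16%, against a nominal 2.5%. Even at a correlation of 0.9 the rate is more than twice nominal.

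These figures assume no true effect on any variable, equal correlation between variables, and a claim that can rest on any single variable. The article gives no correlations, so the range is a sensitivity range and not an estimate for this trial.

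**What to change.** Before unblinding, amend the Statistical analysis section to:

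1. Name one primary variable and one primary AE–LE contrast, tested at two-sided .05. Use the registered primary outcome if there is one. Otherwise choose one now, for example rapid response accuracy at post, adjusted for baseline.
2. Test the other six variables with Holm's procedure. The smallest p-value is then compared with .05/6 = 0.0083.
3. Label follow-up contrasts as supportive.
4. State that the hypothesis is judged on the primary contrast, and replace the blanket alpha sentence accordingly.

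The cost is a change of wording and a stricter threshold for the secondary variables. No extra participants or measurements are needed.

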
### Outcome measurement

A modified lean-and-release technique devised by Bolton and Mansour (2020) will be implemented on land to assess reactive balance immediately before (pre), after (post), and one week after (follow-up) the single bout intervention [25]. Lean-and-release techniques are commonly used to assess reactive balance in various older adult populations [35–37]. This modified lean-and-release technique additionally introduces cognitive factors (i.e., response inhibition and action selection), which are important in certain situations. For safety purposes, participants will wear a harness, which is secured to the ceiling to prevent them from falling in case they fail to recover balance. The participants will then stand with both feet hip-width apart on two separate, parallel force plates (type 9260AA, Kistler AG, Winterthur, Switzerland). A horizontal cable will be attached to the safety harness at the midthoracic level and the other end to the wall behind the participants by a magnet. To simulate a forward fall (trip) situation, the experimenter will instruct participants to lean forward into a support cable while keeping both feet in contact with the floor and to remain relaxed (Fig 2). This position will require dorsiflexion of the ankle, as the rest of the body remains aligned. The forward lean position for each participant, measured by the ankle joint angle, will be determined as the minimal lean angle where a change-of-support reaction (i.e., forward step) is necessary to recover balance upon cable release [38]. Then, the magnet will be deactivated to suddenly release the cable. There are two possible settings: 1) the leg block is placed in front of both legs, and a safety handle is uncovered; or 2) the leg block is removed, and the safety handle is covered. The leg block and handle cover will be controlled via computer-triggered, servo motors. The testing session will be comprised of three blocks: 1) REACH (grasping a safety handle using their right hand while maintaining both feet fixed), 2) STEP (stepping forward using any leg), and 3) RANDOM (random variations of STEP and REACH). To control vision during the third block, participants will wear liquid crystal goggles (Translucent Technologies Inc. Toronto, ON, Canada), that will be closed at the beginning of each trial and opened 400 ms before the cable is released. An experimenter will make careful note of the stepping leg used on each trial, and the participants will be free to step with either leg during testing. The timing of foot-off of the stepping foot will be recorded using the two parallel force plates. A force-sensitive resistor (B&L Engineering, Santa Ana, CA, USA) placed on the top surface of the safety handle and one large force plate in front of the two parallel force plates will be used to detect hand contact with the safety handle during REACH and foot contact during STEP, respectively. To control the predictability of the forthcoming reactions during the third block, the settings will be randomly changed between trials via the data collection program. After sufficient practice trials to familiarize the participants with the stepping and reaching actions, five trials each of the REACH and STEP will be completed, and ten actual trials of RANDOM, including five STEP and five REACH actions in random orders, will be completed. Outcome measurements at post and follow-up will include all randomized participants within the original groups regardless of any discontinuation or deviation from intervention protocols.

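### Multiple imputation is paired with an omnibus ANOVA F or rank tests chosen by assumption checks, so the plan as written does not lead to one combined aquatic-minus-land result

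*Protocol article*

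**What the plan says.** All of the analysis text is in the protocol article, Statistical analysis. The main analysis is a repeated-measures "analysis of variance (ANOVA) with group as a between-group factor and time as a within-group factor", with three time points. It depends on Kolmogorov–Smirnov and Levene checks. If these fail, "Kruskal-Wallis one-way ANOVA will be used for nonparametric variables". Then "post-hoc analyses will be conducted using Tukey post hoc test or Mann-Whitney U test". Baseline enters as a covariate only if the groups differ at baseline.

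On missing data the section says "Missing data will be handled using multiple imputation", and "all statistical analyses taking an intention-to-treat approach will be conducted with SPSS version 25". It also plans estimates: Cohen's d "effect sizes (ES) and confidence intervals (95%) for the parametrical variables", and "probability of superiority for dependent samples" for the nonparametric ones. Alpha is .05 throughout.

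Two other sections bear on how much will be missing. Sample size calculations allows for roughly 15% dropout, taking 38 participants to 44. Outcome measurement says "Outcome measurements at post and follow-up will include all randomized participants within the original groups", whether or not they completed the intervention.

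**The concern.** Multiple imputation produces several completed data sets, and the result has to be combined across them. Rubin's scalar rules combine an estimate and its standard error. The main tests named here deliver an F on 2 degrees of freedom for group × time, an H or a U, and those rules do not take these directly.

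The second difficulty lies in the plan's own logic. The assumption checks choose the test, and they would be run on each completed data set. One data set can call for the ANOVA and another for Kruskal-Wallis on the same outcome. A pooling rule combines the same quantity across data sets, so it cannot combine a group × time F from some with a one-way H from others. Three of the seven outcomes are mini-BESTest scores built on 0-to-2 ratings, so the rank route is a real prospect.

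At stake is whether the intention-to-treat analysis yields one AE minus LE answer per outcome, and how efficiently it uses 44 participants.

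**Working it through.** **Expected missingness.** Inputs from Sample size calculations: 38 evaluable, about 15% dropout, 44 enrolled. 38 × 1.15 = 43.7, which rounds up to the stated 44; 38/0.85 = 44.7 would round up to 45. For a rate given as approximate, 44 is acceptable. The allowance is 44 − 38 = 6 participants (6/44 = 13.6%).

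**Assumptions of the simulations, not given in the documents.** Within-person correlation 0.5–0.7, normal data unless stated, number of imputations m, and the pattern of missing values.

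**Can the planned tests be pooled?** Yes, each needs its own rule.
- Mean differences, including Tukey comparisons: Rubin's rules, total variance = W + (1 + 1/m)B, where W and B are the within- and between-imputation variances.
- Group × time F: it tests k = 2 contrasts with mean estimate q and mean covariance matrix U over imputations, so D1 = q′U⁻¹q / [k(1 + r)], with r = (1 + 1/m)·trace(BU⁻¹)/k and B here the between-imputation covariance matrix.
- Mann-Whitney: the statistic divided by n₁n₂ is the probability of superiority, with null standard error √[(n₁ + n₂ + 1)/(12n₁n₂)] = √[45/(12 × 22 × 22)] = 0.088 at 22 per group. It can be pooled by Rubin's rules, or as a chi-square by D2. Kruskal-Wallis on two groups is equivalent to Mann-Whitney.

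**Simulation with pooling.** 22 per group, 6 participants missing post and follow-up completely at random, correlation 0.6, m = 20, no true effect, 1,500 runs:

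| Analysis | Type I error at nominal 5% |
|---|---|
| Interaction F, D1 | 5.3% |
| Mann-Whitney, D2 | 4.9% |
| Mann-Whitney, Rubin's rules on probability of superiority | 4.9% |
| Interaction F, one imputed data set read alone | 9.7% |

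The simulation standard error at 5% is √(0.05 × 0.95/1,500) = 0.6 points, so the three pooled tests are compatible with 5%. The separate p-values lay on both sides of .05 in 23% of trials (F) and 20% (Mann-Whitney). That shows why pooling is needed; it is not an error rate.

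**Simulation without pooling.** 15% of follow-up values missing, m = 5, 6,000 runs per setting. Analysing one completed data set, or the mean of five, as if observed gave 7.3–8.0% for the interaction F and 6.6–8.5% for follow-up comparisons.

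**Does the choice of test vary between imputations?** 6 follow-up values missing, m = 5, correlation 0.5 or 0.7, Lilliefors-corrected Kolmogorov–Smirnov check by group and visit, Levene by visit. The five data sets disagreed on the test in about 14–20% of trials per outcome, with normal or mildly skewed data.

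**What would one model gain?** 22 per group, 6 follow-up values missing, correlation 0.5–0.6, true difference 0.8 SD at both visits. A joint test from a baseline-adjusted mixed model had about 91–93% power, against 76–83% for the validly pooled interaction F. Type I error was near 5–6% for both. The reason is mainly baseline adjustment. With unit variance and correlation ρ, a change from baseline has variance 2(1 − ρ), and a baseline-adjusted outcome has 1 − ρ². At ρ = 0.5 these are 1.00 and 0.75; at ρ = 0.6 they are 0.80 and 0.64.

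**The case against.** A reader might infer that these tests cannot be pooled at all and that no valid intention-to-treat test exists. The documents do not support that: every named test has a valid pooling route, and the pooled versions held their level. The plan also schedules effect estimates, so its outputs are not only test statistics.

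A reader might also infer that the trial will run at 7–8% type I error. That figure belongs to analysing one completed data set, or averaged imputations, as observed. The article says multiple imputation and nowhere proposes either shortcut.

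The pooling rule, the imputation model and the number of imputations are details that a condensed article commonly leaves to a statistical analysis plan, so their absence alone is no fault. Missingness may also fall below 15%, since post testing follows a single session immediately, follow-up is one week later, and the article intends to measure everyone randomised.

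All of this stands. What it does not answer is the data-driven switch between tests: a later pooling rule cannot combine an F with an H, so the selection rule itself would have to be changed. It also leaves untouched that a simpler and more powerful analysis of the same data is available.

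**Conclusion.** The point holds in limited form. The plan joins multiple imputation to an omnibus F or rank tests and lets assumption checks choose between them. As written this does not lead to one combined AE minus LE result. The plan is poolable, and no inflation of type I error is established. The measurable loss is efficiency: roughly 76–83% power for the properly pooled interaction F, against 91–93% for a baseline-adjusted mixed model. This rests on the assumed correlation, missingness and 0.8 SD effect at both visits. Most of the gain comes from always adjusting for baseline, not from dropping imputation as such. No sample-size figure changes.

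**What to change.** For the four continuous outcomes (hand contact, foot-off and foot contact times, and rapid response accuracy), replace imputation plus repeated-measures ANOVA with one likelihood-based mixed model on all available post and follow-up data. Include group, visit, group × visit and baseline always, with an unstructured covariance. Report the AE minus LE difference with a 95% confidence interval at each visit. This handles dropout under missing at random without imputation.

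For outcomes analysed by ranks, such as the three mini-BESTest scores, fix the test in advance. If imputation is kept, pool the between-group probability of superiority and its standard error; do not read test results from separate data sets. The measure the article names is for dependent samples, so the between-group version should be stated.

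Cost: a few sentences of analysis text and slightly more analysis work, in the same software, with no new data. Downsides: the model assumes normality for the continuous outcomes, and a participant with neither post nor follow-up data contributes nothing to it, which should be stated beside the intention-to-treat claim.
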